## Abstract

**Background::**

Heroin addiction remains a significant public health problem worldwide, and relapse to heroin use following cessation of agonist maintenance treatment is common. The problems associated with use of opioid agonists mean that non-opioid therapies need to be developed to ameliorate acute and protracted opioid withdrawal syndromes.

**Methods::**

Fifteen men with opioid use disorder on methadone maintenance treatment have been enrolled from an addiction treatment center as an experimental group in this case-controlled study. This group is receiving laser meridian massage on the back, including the Bladder meridian and Governor Vessel, 3 times weekly for 4 weeks. An age-matched control group that does not receive laser meridian massage has also been enrolled. Urinary morphine levels are being checked before and after 2 and 4 weeks of treatment. Subjects are requested to self-report their number of episodes or days of heroin use and 0 to 10-point visual analogue scale scores for heroin craving/refusal to use heroin during the previous week before and after 2 and 4 weeks of treatment. Quality of life will be reported using the Short Form-12v2 before and after 4 weeks of treatment. Pulse diagnosis will be recorded and heart rate variability calculated after one single treatment session. The baseline patient characteristics will be compared between the experimental and control groups using the independent *t* test and Chi-square test. Data are compared between the 2 groups using repeated-measures analysis of variance, generalized estimating equations, and the paired *t* test.

**Objective::**

To investigate the effect of adjuvant laser meridian massage in men with opioid use disorder on methadone maintenance treatment.

**Trial registration::**

ClinicalTrials.gov NCT04003077.

## Introduction

1

Opioid use disorder (OUD), which most commonly manifests as heroin addiction, remains a significant public health problem worldwide. Clinically, OUD is characterized by physical dependence, as evidenced by tolerance and withdrawal, and by psychological symptoms, including drug cravings, depression, anxiety, and inability to control use of heroin.^[1]^ Methadone maintenance treatment is the most widespread and extensively researched treatment for heroin addiction. Methadone maintenance has been shown to reduce the frequency of opioid use, reduce mortality, reduce the transmission of human immunodeficiency virus and viral hepatitis, improve employment prospects, and reduce the frequency of criminal behavior. Many of these positive effects are strongly associated with higher daily methadone dose and with increasing duration of treatment.^[2]^ However, relapse to heroin use following cessation of agonist maintenance treatment is common. Research is lacking on when, who, and how to withdraw from opioid agonist maintenance treatment. The problems associated with use of opioid agonists have made it necessary to develop non-opioid therapies to ameliorate the symptoms of acute and protracted opioid withdrawal.^[3,4]^

Acupuncture is becoming a popular complementary and alternative treatment in Western countries and is growing in popularity worldwide.^[5,6]^ Acupuncture is based on traditional Chinese medicine (TCM) theory and was developed according to the principle that human bodily functions are controlled by the “meridian” and “Qi and blood” systems. There are 365 designated acupuncture points located along 14 meridians that can be used to stimulate, balance, and harmonize the yin and yang by relieving blockages in the flow of Qi.^[7]^ This method of healing has been used to promote homeostasis of the body's organs.

## Methods

2

### Ethics approval

2.1

The study was approved by our institutional human ethics committee (Chang Gung Medical Foundation Institutional Review Board, approval number 201801823A3). The protocol was registered with ClinicalTrials.gov (identifier NCT04003077). Written informed consent will be obtained from all study participants. Personal information about potential and enrolled participants will be collected, shared, and maintained in an independent closet in order to protect confidentiality before, during, and after the trial.

### Study design

2.2

This case-controlled study is being performed in the Department of Psychiatry and Chinese Medicine at Kaohsiung Chang Gung Memorial Hospital. The study was started in February 2019 and will continue until February 2020. Subjects recruited from our institution's addiction treatment center are being allocated to the experimental group (laser meridian massage plus methadone maintenance treatment, n = 15, expected). The study participants will receive 12 sessions of laser meridian massage three times weekly for 4 weeks. An age-matched control group of subjects who do not receive laser meridian massage (methadone maintenance treatment only, n = 15, expected) will also be enrolled. The study design is shown in Figure 1.

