### Participants

2.3

A diagnosis of OUD is confirmed using the diagnostic criteria of the Diagnostic and Statistical Manual of Mental Disorders, Fifth Edition. Male subjects aged 20 to 70 years with OUD who have received methadone maintenance treatment for at least 1 month and provided informed consent are being recruited. Psychiatrists assess each prospective participant's eligibility to be enrolled in the study. Subjects with a critical illness or human immunodeficiency virus infection, those on antidepressant or antipsychotic medication, those who have taken Chinese herbs or received acupuncture treatment during the previous 30 days, those who are unsuitable for recruitment in the opinion of the attending physician, and those who are unwilling to provide informed consent are excluded.

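### The laser and control groups are not described as randomised, are matched on age only and have no adjustment named, so a difference between them cannot be credited to the laser

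*Protocol article*

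**What the plan says.** Section 2.2 (Study design) of the Protocol article opens with "This case-controlled study is being performed in the Department of Psychiatry and Chinese Medicine". On the experimental arm it says "Subjects recruited from our institution's addiction treatment center are being allocated to the experimental group". The comparator is "An age-matched control group of subjects who do not receive laser meridian massage", specified as "methadone maintenance treatment only, n = 15, expected". The Abstract gives the same structure. The text shown mentions no random mechanism, and age is the only matching factor named.

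Section 2.3 (Participants) asks that men have "received methadone maintenance treatment for at least 1 month". It sets no upper limit on duration and no dose criterion.

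Section 1 (Introduction) states "Methadone maintenance has been shown to reduce the frequency of opioid use", lists further benefits, and adds: "Many of these positive effects are strongly associated with higher daily methadone dose and with increasing duration of treatment".

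Section 2.7 (Statistical analysis) compares baseline characteristics with t and chi-square tests. For the group comparisons it then lists t, McNemar, repeated-measures ANOVA, GEE and paired t procedures. It names no covariate, and nothing follows if a baseline difference is found. The objective, in the Abstract and at the end of the Introduction, is the effect of the adjuvant laser treatment.

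**The concern.** The question is causal, but the groups are formed in different ways. One is filled by recruiting men to 12 sessions over 4 weeks; the other is assembled afterwards by age. Men prepared to attend three times a week may be more motivated to stop using heroin, and the plan has no measure of that.

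The article also identifies two prognostic factors and then leaves both free to differ between groups. Both primary outcomes, urinary morphine and self-reported heroin use, measure opioid use, which is one of the benefits that the Introduction lists for methadone. A man in his second month of methadone and a man several years into it are equally eligible, and age matching does not balance them.

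If the groups differ on such factors, the difference could be reported as a laser effect on both primary outcomes. The case-controlled label hides this. Every participant has the disorder and the groups are defined by treatment, so this is a non-randomised controlled study.

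**Working it through.** **1. Which comparison the sample size rests on.** Inputs: f = 0.25, α = 0.05, power 0.80 (section 2.4); 2 groups (2.2); m = 3 measurements (2.6). A correlation between visits of ρ = 0.5 and sphericity are assumptions, since the article states neither.

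- Group-by-time interaction: λ = f²·N·m/(1 − ρ) = 0.0625 × 28 × 3 / 0.5 = 10.5, with 2 and 52 degrees of freedom. Power is 0.812, so the stated 28 reproduces.
- With ρ = 0.3 the same test needs 38; with ρ = 0.7 it needs 18.
- The between-group main effect at ρ = 0.5 needs 86.
- Dropout: 28 × 1.07 = 29.96, which gives the stated 30.

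The sample size is not in dispute. The calculation matters because it points to group-by-time as the intended comparison.

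**2. The baseline tests as a safeguard.** Two-sample t test, n = 15 per group, two-sided 0.05, 28 degrees of freedom, noncentrality k·√(n/2) = k × 2.739 for an imbalance of k SD.

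- k = 0.5: noncentrality 1.37, power 0.262.
- k = 0.8: noncentrality 2.19, power 0.562.
- With 14 per group: 0.247 and 0.531.

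An imbalance of half an SD would be missed about three times in four.

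**3. An unadjusted comparison of outcome levels.** Let a confounder correlate r with the outcome and differ by k SD between groups, and let the laser do nothing. The bias is r·k SD. The article gives no distribution of dose or duration, so r and k are assumptions. Rejection rates with 15 per group, against a nominal 5%:

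| r | k = 0.5 | k = 0.8 |
|---|---|---|
| 0.3 | 6.8% | 9.7% |
| 0.5 | 10.1% (bias 0.25 SD) | 18.5% (bias 0.40 SD) |
| 0.7 | 15.3% | 31.6% |

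**4. The group-by-time comparison.** A shift of the same size at all three visits drops out of every change from baseline. It adds nothing to the interaction, and the rate stays at 5%. Bias arises only if the confounder alters the 4-week course. The result depends on how large an interaction it creates (N = 30, ρ = 0.5, 2 and 56 degrees of freedom):

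- f = 0.0625, a quarter of the design effect: λ = 0.0039 × 30 × 3 / 0.5 = 0.70; rejection rate 10.4%.
- f = 0.125, half the design effect: λ = 0.0156 × 30 × 3 / 0.5 = 2.81; rejection rate 28.9%.

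These two values of f are illustrations. The documents do not show how large such an interaction would be.

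**5. Can allocation still be changed?** The Abstract reports both groups as already enrolled. Section 2.2 gives both sizes as expected and puts enrolment of the controls in the future. The two statements leave this open.

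**The case against.** The strongest reply is that the outcomes are measured before treatment and the intended test concerns change, so differences in starting level are already handled. That stands for stable differences, and it limits the figures in step 3 to comparisons of levels. It does not cover factors that shape the 4-week course. Time on methadone, dose and motivation could each do so.

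A second reply is that GEE can carry covariates and that an analysis plan not shown may name them. That also stands: a reader might infer that the analysis is definitely unadjusted, but the article supports only that no adjustment is named. The non-random, age-only allocation is stated in the article itself, however, and no later document can adjust for motivation that is not measured.

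Third, a reader might take the Introduction to say that dose and duration drive heroin use. It reports an association, and for many of a list of benefits that also includes mortality, infection, employment and crime.

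Fourth, a reader might infer that both groups come from the same clinic and that randomising them is a simple amendment. The article gives a source only for the experimental group, and enrolment may be complete. Restriction to men and the exclusions for psychiatric medication, recent acupuncture and Chinese herbs do control some other factors.

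**Conclusion.** The concern holds as a limit on causal attribution. Allocation is not described as random, matching is on age alone, and the two prognostic factors that the article names are neither restricted (beyond the 1-month minimum) nor listed for adjustment. The baseline tests would miss a 0.5 SD imbalance 74% of the time and a 0.8 SD imbalance 44% of the time.

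The size of any bias is not known. For an unadjusted comparison of levels, the false-positive rate is about 10% to 18% if r = 0.5 and the imbalance is 0.5 to 0.8 SD. A reader might carry that range over to the planned group-by-time test. The documents do not support this, because a constant shift cancels there. Inflation of that test requires a confounded difference in trajectory, whose size can only be assumed.

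The absence of randomisation is itself a reading of the text (age-matched controls, enrolled separately), and the flowchart is not shown. That reading is secure enough to act on.

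**What to change.** 1. Prespecify one primary model for the 2- and 4-week outcomes, for example the GEE already planned. Adjust it for the baseline value of the outcome, daily methadone dose at entry and months on methadone at entry.
2. Describe the study as a non-randomised controlled study and drop the case-controlled label.
3. Word the conclusion as an association. Adjustment cannot remove differences in unmeasured motivation.
4. State whether enrolment is still open and where the controls come from. Randomisation is an option only for men not yet enrolled. Any men randomised later would need to be analysed separately from those already allocated.

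Cost: about 3 degrees of freedom (one per covariate), methadone dose and start date from clinic records, and changes of wording. Items 1 to 3 need no extra participants.

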**Figure 1 F1:**
[figure not shown]
Flowchart showing movement of subjects through the study.

### Participants

2.3

A diagnosis of OUD is confirmed using the diagnostic criteria of the Diagnostic and Statistical Manual of Mental Disorders, Fifth Edition. Male subjects aged 20 to 70 years with OUD who have received methadone maintenance treatment for at least 1 month and provided informed consent are being recruited. Psychiatrists assess each prospective participant's eligibility to be enrolled in the study. Subjects with a critical illness or human immunodeficiency virus infection, those on antidepressant or antipsychotic medication, those who have taken Chinese herbs or received acupuncture treatment during the previous 30 days, those who are unsuitable for recruitment in the opinion of the attending physician, and those who are unwilling to provide informed consent are excluded.

### Sample size

2.4

A sample size of 28 was calculated to be needed based on 2-way repeated-measures analysis of variance with a medium effect size of 0.25, a significance level (α) of 0.05, and a desired power (1−β) of 0.80.^[13]^ Anticipating a 7% dropout rate, a total of 30 study participants will need to be recruited.

### Interventions

2.5

The study participants will receive 12 sessions of laser meridian massage three times weekly for 4 weeks using a gallium aluminum arsenide LaserPen (maximal power, 150 mW; wavelength, 810 nm; area of probe, 0.5 cm^2^; power density, 300 mW/cm^2^; pulsed wave; and frequencies [Bl, 667 Hz; B4, 4796 Hz]; RJ-Laser, Reimers & Janssen GmbH, Waldkirch, Germany). The laser treatment will be applied to the back, including the Bladder meridian (BL11–BL25) and Governor Vessel (GV3–GV14; Figs. 2 and 3) for 15 minutes, to deliver a total treatment dose of 67.5 J/cm^2^. The laser treatment will be applied by the same experienced physician who has adequate training and is a licensed Chinese medicine practitioner in Taiwan. The physician and patients are required to wear protective goggles to inhibit visual perception during laser meridian massage.

**Figure 2 F2:**
[figure not shown]
Meridians used for heroin addiction: Bladder meridian (BL11-BL25) and Governor Vessel (GV3-GV14).

**Figure 3 F3:**
[figure not shown]
Laser meridian massage performed using the LaserPen device at the Governor Vessel.

### Outcome measurements

2.6

Outcome measures will include subjective reporting of heroin use and quality of life and objective urinary morphine levels. The primary outcomes are urinary morphine levels and self-reported times or days of heroin use during the previous week before and after 2 and 4 weeks of treatment. The secondary outcomes are self-reported visual analogue scale (VAS) scores for heroin craving/refusal to use heroin (0–10 points) in the previous week before and after 2 and 4 weeks of treatment and quality of life using the Short Form-12v2 (SF-12v2) before and after 4 weeks of treatment. The participant's pulse diagnosis and heart rate variability after one single treatment session are also being recorded.

A VAS score of 0 for heroin craving indicates no heroin craving and a score of 10 indicates the strongest possible heroin craving. A VAS score of 0 for refusal to use heroin indicates no refusal and a score of 10 indicates total refusal. The SF-12v2 Health Survey is a multipurpose, short-form health instrument containing 12 questions that yields an 8-scale profile of functional health and well-being (Physical Functioning [PF], Role-Physical [RP], Bodily Pain [BP], General Health [GH], Vitality [VT], Social Functioning [SF], Role-Emotional [RE], Mental Health [MH]), as well as two psychometrically-based physical and mental health summary measures and a preference-based health utility index. The PRO CoRE, which is part of the Smart Measurement System suite of products and Optum's upgrade to the QualityMetric Health Outcomes scoring software, will be used to score the SF-12v2 Health Survey.

The reasons for patients not completing their follow-up visits or dropping out of the study, such as adverse events/intercurrent illnesses, suboptimal response to therapy, failure to return for follow-up, failure to meet the selection criteria at entry, other protocol violations, and refusal to receive treatment, are recorded, as are potential adverse events.

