### Statistical analysis

2.7

The data will be presented as the mean ± standard deviation. The independent *t* test and chi-square test will be used to evaluate and compare the baseline patient characteristics between the experimental and control groups. The independent *t* test and McNemar test will be used to compare the differences between 2 groups. Repeated-measures analysis of variance, generalized estimating equations, and the paired *t* test will be used for comparisons between the 2 study groups. All analyses will be performed using SPSS for Windows, version 22 (Statistics 22, IBM Corp., Armonk, NY). A *P* value < .05 will be considered statistically significant.

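### Two primary outcomes share one undivided 0.05: if either may count as success, the false-positive chance is about 8 to 10%, and higher if visits or methods are tested separately

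*Protocol article*

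**What the plan says.** **Outcomes.** Outcome measurements (2.6) names two primary outcomes: "The primary outcomes are urinary morphine levels and self-reported times or days of heroin use during the previous week". Both are taken at three times, "during the previous week before and after 2 and 4 weeks of treatment", which gives two post-baseline visits. The section does not say whether success needs one outcome or both, or which visit decides. It describes urinary morphine as objective and heroin use as subjectively reported.

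**Tests.** Statistical analysis (2.7) gives two lists for comparing the groups. The first pairs the independent t test with McNemar: "McNemar test will be used to compare the differences between 2 groups". The second reads: "Repeated-measures analysis of variance, generalized estimating equations, and the paired *t* test will be used for comparisons between the 2 study groups". No test is tied to an outcome or a visit. One rule covers all of them: a P "value < .05 will be considered statistically significant".

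**Size.** Sample size (2.4) uses one 2-way repeated-measures ANOVA with effect size 0.25, "a significance level (α) of 0.05" and "a desired power (1−β) of 0.80". This gives 28 participants, raised to 30 for 7% dropout. It names no outcome and does not divide the 0.05.

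**The concern.** The sample size spends the whole 0.05 on one test, while the outcome section offers two primary results and the analysis section judges each at the full 0.05. These fit together only if one outcome carries the claim, or if both must succeed. The article states neither. Read as written, a significant result on either outcome could be reported as success on a primary outcome, and the 5% error rate would not apply to that claim. With about 15 men per group, a false positive on one outcome would be hard to tell from a real effect. This goes beyond missing detail, because the threshold, the two primaries and the undivided alpha are all stated.

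**Working it through.** **Inputs from the article:** two primary outcomes; baseline, week 2 and week 4 (m = 3); two groups of 15 expected; effect size f = 0.25; alpha 0.05; power 0.80; N = 28 before dropout. **Assumed:** the correlation between visits (ρ) and the correlation between outcomes, neither of which the article gives.

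**1. Reproduce the sample size.** For the group-by-time interaction under sphericity, λ = f²·N·m/(1 − ρ), with m − 1 and (N − 2)(m − 1) degrees of freedom. With ρ = 0.5:

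λ = 0.0625 × 28 × 3 / 0.5 = 10.5, df 2 and 52, power 0.812.

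N = 28 is the smallest even total that reaches 0.80, so the figure reproduces. For dropout, 28/0.93 = 30.1 and 28 × 1.07 = 29.96, in line with 30. The 0.05 is therefore fully used by one ANOVA.

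**2. Simple bounds if either outcome may count.**
- Two tests, independent: 1 − 0.95² = 9.75% (at most 2 × 5% = 10%).
- Two outcomes at two visits, four tests, independent: 1 − 0.95⁴ = 18.5% (at most 4 × 5% = 20%).

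Anything above 20% therefore needs tests beyond outcome by visit.

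**3. Simulation under no effect.** Normal data and 20,000 runs per setting, with 14 per group (28/2) and both correlations varied from 0 to 0.8:

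| Tests that may each count as success | Chance of at least one false positive |
|---|---|
| One ANOVA interaction per outcome | 8.5 to 10.1% |
| t tests on visit values, weeks 2 and 4 | 12.4 to 18.3% |
| t tests on changes, weeks 2 and 4 | 14.2 to 17.7% |
| ANOVA plus change t tests | 15.6 to 19.2% |
| ANOVA plus visit-value t tests | 19.1 to 23.9% |
| ANOVA plus both kinds of t test | 25.3 to 31.2% |

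A second simulation had 15 per group, visit correlation 0.5 and outcome correlation 0 to 0.8. It gave 8 to 9% for one ANOVA per outcome, 14 to 17% for change t tests at both visits, and 17 to 21% for any of ANOVA, GEE or those t tests.

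**4. GEE alone, one outcome.** With an uncorrected sandwich variance and a chi-square reference, the interaction test rejected in 8 to 9% of null trials at 15 per group. The article states neither the variance estimator nor the reference distribution, so this describes one possible implementation.

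**5. Price of the alternatives** (same formula, ρ = 0.5).
- Alpha 0.025 for each outcome: power 72.1% at N = 28, and N = 34 is needed for 80%.
- Both outcomes required at 0.05: the error stays at or below 5%. If each has the stated power of 0.80, joint power is 0.80 × 0.80 = 0.64 when the outcomes are independent, rising towards 0.80 as they move together.

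**The case against.** The strongest reply is that the analysis section is a pooled list serving all outcomes, including the visual analogue scores and the SF-12v2. It does not say that each method is run on each primary outcome or that weeks 2 and 4 are tested separately. The one test tied to the design is the repeated-measures ANOVA, which takes all visits together. A full protocol or analysis plan that is not shown might also name the deciding comparison, and if both outcomes must succeed, no alpha needs to be split.

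Much of this stands, and it limits the size of the point. A reader might infer that the plan's error rate simply is 16 to 21%, or that analysts will choose among outcomes, visits and methods once they have seen the data. The article does not support either inference, since those figures need separate visit tests, and the upper end needs several methods as well. A reader might also infer that the planned GEE is too liberal, but its settings are not given. The 81% power is a recalculation at an assumed correlation of 0.5, while the stated figure is 80%. Whether self-report is open to bias is a separate matter from multiplicity.

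The reply does not remove the core. Even on its most favourable either-outcome reading, one ANOVA per outcome, the error is nearly double the nominal 5%. The reading under which 5% holds, that both outcomes must succeed, is nowhere stated, and its joint power is not what the sample size describes.

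**Conclusion.** The point holds in a limited form. Two primary outcomes are each judged at 0.05 with no success rule, against a sample size that allows for one test. If either outcome may count, the false-positive chance is about 8 to 10% with one ANOVA per outcome. That is the figure to rely on, because it uses only the test behind the sample size. About 12 to 18% applies if weeks 2 and 4 are tested separately. About 17 to 21% applies if ANOVA, GEE and change t tests may all count, and more if they are used more freely. These two ranges show where the open wording could lead. They do not describe what the article commits to.

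The ranges assume normal data, the stated correlations and two groups that differ only by chance. The point should be corrected before analysis, but it does not undermine the design.

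**What to change.** Name urinary morphine as the single primary outcome. Test it once at two-sided 0.05 by one pre-specified group comparison, for example the group-by-time test used for the sample size or a baseline-adjusted comparison at week 4. If the week 4 comparison is chosen, restate the power for it. Test self-reported use next, at 0.05, only if the primary succeeds. Label other visits and methods as supportive.

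If both outcomes must stay primary, there are two routes:
- Require both to succeed, and state the joint power.
- Use Holm or 0.025 for each, and restate the power: about 72% at N = 28 for 0.025, assuming a within-subject correlation of 0.5, against the stated 80%.

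If GEE is used for a primary outcome, specify a small-sample-corrected variance with a t or F reference.

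**Cost.** The recommended route needs no extra participants. Self-reported use loses co-primary status. Because the study began in February 2019 and is registered, the change should be made without sight of outcome data by group and documented as a dated amendment.
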